#### Surgical technique

Colectomies for lesions located between the cecum and splenic flexure are performed using a five-port technique, and the specimen is extracted through a periumbilical incision obtained by extending the camera port or by a transverse suprapubic incision. Anterior resection, sigmoid, and left hemicolectomy are performed using a four-port technique, and the specimen is removed through a periumbilical or transverse suprapubic incision. An additional 11-mm suprapubic trocar is generally used in low anterior resection to optimize surgical field exposure. Loop ileostomy is reserved for cases in which a total mesorectal excision is performed.

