### Outcome measures

#### Primary endpoint

To demonstrate the noninferiority of WI compared with WI plus L-TAP for pain control in the early postoperative period after laparoscopic colorectal resection. The pain control is evaluated at 6 hr from surgery considering the greatest intensity of pain at rest and during cough, according to NRS. The NRS is graded from 0 to 10, where 0 refers to “no pain” and 10 to “worst pain.”

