### Sample size calculation

The null hypothesis is that WI is inferior to WI plus L-TAP. To test the alternative hypothesis of noninferiority of WI compared with WI plus L-TAP, the sample size is calculated using the mean value of NRS. Considering our results with previously treated patients, the mean (standard deviation [SD]) pain intensity score according to NRS is 2.8 (1.9) for the WI plus TAP block group and 3.1 (1.9) for the WI group. These data have been used for the sample size calculation. The noninferiority limit of NRS 1 has been intended to be the largest difference that is clinically acceptable, so that a difference greater than 1 would matter in practice. A two-sided sample size calculation with 0.8 power and significance level of 0.05 reveals that 100 patients have to be included. With an estimated dropout rate of 8%, a sample size of 108 patients is required with 54 patients in the WI group and 54 patients in the WI plus L-TAP group. Patient recruitment is split between the two centers. Sample size has been calculated using PASS® version 14.0.8 with a noninferiority test for the difference of two means.

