### Allocation

Patients satisfying the inclusion criteria and willing to enter the study are randomized to one of the two study arms after signing the informed consent. The randomization is performed blindly in a 1:1 fashion. The allocation to WI group or WI plus L-TAP group is achieved by creating a randomization list that includes a maximum of six subjects for nine blocks. The randomization list has been obtained by using an online program available at https://www.sealedenvelope.com/simple-randomiser/v1/lists. A separate list has been created for each center so that 54 patients are recruited at the Division of General and Hepatobiliary Surgery, University of Verona Hospital Trust, Verona, Italy, and 54 patients at the Colorectal Cancer Center, Kyungpook National University Medical Center, Kyungpook National University, Daegu, Korea. Similarly, each center collects the data separately after identifying the patients with an alphanumeric code.

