### Data collection and management

A trained member from each surgical staff is in charge of data collection. Baseline demographics, as well as preoperative, intraoperative, and postoperative variables, are collected using a specifically created datasheet and stored in a specifically created dataset. The same datasheet and dataset are used in the two centers (Additional file 2).

Furthermore, to reduce as much as possible the variability among patients in reporting pain intensity, the patient is instructed on use of the NRS by the same member of the surgical staff at the time of accrual (15–20 days before surgery) and the day before surgery. To reduce the variability related to data collection, the same member will collect all other investigated variables.

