### Statistical analysis

Statistical analyses will be performed on an intention-to-treat (ITT) basis using IBM SPSS Statistics software version 21.0 (IBM Corporation, Armonk, NY, USA). Because the ITT analysis includes all randomized subjects and, in this study**,** there may be up to 6% missing data, an imputation method will be established. A per-protocol (PP) analysis will also be performed. In noninferiority studies, both ITT and PP analyses are recommended and should support the noninferiority hypothesis. Continuous variables are summarized as mean and SD or as median and 95% confidence interval (95% CI) if the distribution is asymmetrical. Categorical variables are summarized as numbers and percentages. The categorical variables will be compared between groups with the chi-square test or Fisher’s exact test, depending on the number of events. The continuous variables will be compared between groups using an unpaired *t* test or the Mann-Whitney *U* test, depending on data representation. A two-sided *P* value less than 0.05 will be considered significant.

The primary outcome considers the level of pain at 6 hr from surgery graded according to the NRS. Assuming a pain score difference of 1 of 10 to be clinically significant, noninferiority is determined when the lower boundary of the 95% CI is > 1. Superiority, on the other hand, is determined when the two means are significant at the 5% level (two-sided *P* < 0.005).

The secondary objectives aim at assessing the benefits of choosing one procedure over the other. Descriptive statistics and plots will be used to compare the two groups, taking into account: (1) pain intensity scores at 12, 24, 36, 48, and 72 hr after surgery; (2) the quantity of rescue analgesic drugs consumed from the day of surgery until POD 3; (3) the occurrence of PONV; (4) the occurrence of PPOI; (5) the time needed to restore bowel function considered as the time needed to pass gas and stool as well as to tolerate a liquid and solid diet; and (6) the length of hospital stay.

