## Trial status

Recruitment started on April 8th, 2018, and was completed on March 31st, 2019. (UniVR CESC-1509; KNUMC 2017-11-020-002).

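### Cheap improvement: the 6 h pain comparison is unadjusted, and a prespecified linear model with center and a few pre-allocation covariates could modestly narrow its interval

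*Protocol article*

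**What the plan says.** All references are to the protocol article.

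- **Primary endpoint:** "The pain control is evaluated at 6 hr from surgery considering the greatest intensity of pain at rest and during cough, according to NRS".
- **Statistical analysis:** "The continuous variables will be compared between groups using an unpaired" t test or a Mann-Whitney test, according to the data. The primary outcome is judged by a 95% CI against a difference of 1 point. No other model is named for it.
- **Allocation:** "A separate list has been created for each center so that 54 patients are recruited at the Division of General and Hepatobiliary Surgery", with the other 54 at the Korean center on their own list. Setting adds that one surgeon per center performs every procedure, so center and surgeon coincide.
- **Data collection and management:** "Baseline demographics, as well as preoperative, intraoperative, and postoperative variables, are collected using a specifically created datasheet". The datasheet is Additional file 2, which is not shown here.
- **Sample size calculation:** means and SDs of "2.8 (1.9) for the WI plus TAP block group and 3.1 (1.9) for the WI group", and "The noninferiority limit of NRS 1 has been intended to be the largest difference that is clinically acceptable".
- **Trial status:** "Recruitment started on April 8th, 2018, and was completed on March 31st, 2019".

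**The concern.** The conclusion turns on whether a confidence interval clears a fixed 1-point margin, so the width of that interval matters directly. Accrual is closed, so width cannot be bought with more patients. Two sources of explainable variation are left in the error term. One is center, which the design separates by list but the analysis ignores. The other is whatever the baseline and preoperative data explain of pain at 6 h.

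A linear model that uses them still estimates the difference in means, which is the scale of the margin and of the sample size calculation. If these variables carry information about 6 h pain, the unadjusted comparison gives up precision that would cost no patients to recover.

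**Working it through.** **Inputs from the article:** 54 per arm (N = 108), SD 1.9, expected difference 3.1 − 2.8 = 0.3 against WI, margin 1, 95% CI.

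**Inputs assumed:** R-squared of 0 to 0.20 between the covariates (center included) and 6 h NRS. The article gives no value. The model has k = 5 parameters beyond arm: two for a three-level resection type, and one each for age, sex and center.

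**1. The plan's own figure.** Per arm, n = 2 × 1.9² × (1.960 + 0.842)² / (1 − d)².
- At d = 0.3: 56.67 / 0.49 = 115.7, so 116 per arm and 232 in total.
- At d = 0: 56.67, so 57 per arm and 114 in total.
- With one-sided 0.05 the totals are 184 and 90.

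None of these gives the stated 100 evaluable patients. The check below therefore takes the 54 per arm as given.

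**2. Unadjusted analysis.**
- SE = 1.9 × √(2/54) = 0.3657, with df = 106 and t = 1.983.
- Half-width = 1.983 × 0.3657 = 0.725.
- Noncentrality = (1 − 0.3) / 0.3657 = 1.914.
- Power = P(noncentral t > 1.983) = 47.5%.

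**3. Adjusted analysis, with the cost of fitting charged.**
- SE = 1.9 × √(1 − R²) × √(2/54) × √(1 + k/(N − k − 3)).
- The last factor is √(1 + 5/100) = √1.05, the expected price of chance imbalance in the fitted terms.
- df = 106 − 5 = 101 and t = 1.984.

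| R² (assumed) | SE | Half-width | Noncentrality | Power at 0.3 |
|---|---|---|---|---|
| unadjusted | 0.3657 | 0.725 | 1.914 | 47.5% |
| 0 | 0.3747 | 0.743 | 1.868 | 45.6% |
| 0.05 | 0.3652 | 0.724 | 1.917 | 47.6% |
| 0.10 | 0.3555 | 0.705 | 1.969 | 49.6% |
| 0.20 | 0.3351 | 0.665 | 2.089 | 54.3% |

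Break-even is at R² of about 0.05. At 0.10 the interval is about 3% narrower (0.705/0.725 = 0.972), and at 0.20 about 8% narrower (0.665/0.725 = 0.917). Without the charge for fitting, power would be 51.6% and 56.4% at 0.10 and 0.20, about 2 points too favorable.

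**4. What adjustment cannot do.** With the 50 evaluable per arm that the plan expects, unadjusted power at 0.3 is 44.6%. Reaching 80% there would need R² = 1 − [0.7 / (2.802 × 1.9 × √(2/50))]² = 1 − (0.7/1.065)² ≈ 0.57 (normal approximation, no charge for fitting).

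**The case against.** The strongest reply is that nothing here is wrong. An unpaired comparison of randomized arms is valid, and its interval already allows for chance imbalance. This stands, and it limits the point to efficiency. A covariate list may also sit in an analysis plan that is not shown. But the article names the test itself, so the suggestion concerns a stated method and not a missing detail.

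A reader might go further in four ways that the article does not support.

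- **That the planned resection fixes the wounds.** Surgical technique allows a periumbilical or a suprapubic extraction for proximal and left-sided resections alike. It also says only "An additional 11-mm suprapubic trocar is generally used in low anterior resection", which would bring that operation from four ports to the five used for a proximal colectomy.
- **That age, sex and planned resection type are known to be on the datasheet and to be prognostic.** The datasheet is not shown. Age appears only as an eligibility limit, sex is not mentioned, and planned resection type is not named as a recorded item. Nothing in the article says that any of the three predicts 6 h pain.
- **That adjustment is the only way left to narrow the interval.** The article does not establish this.
- **That removing chance imbalance is an extra benefit.** An evenly split baseline factor would differ between arms with an SD of √(0.25 × 2/54) = 9.6 percentage points, but that variation is already counted through R-squared.

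Timing is a fair caution too. The 6 h scores existed when the article was published in July 2019, and surgical staff collect them. The article does not say whether they had been examined by arm.

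**Conclusion.** The point holds as an optional, low-cost improvement. The analysis as written omits center, which the randomization separates, and uses no baseline covariate. A prespecified linear model could narrow the interval judged against the margin.

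The effect is modest and could go either way. Relative to 47.5% unadjusted, it runs from a loss of about 2 power points at R-squared 0, through no change at about 0.05, to gains of about 2 points at 0.10 and 7 points at 0.20. These figures rest on 54 analyzed per arm, SD 1.9, a true difference of 0.3, five fitted parameters and assumed R-squared values. Part of any R-squared may come from center alone, which is the covariate with the firmest footing in the article.

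It would be wrong to read this as an invalid analysis or as a remedy for low power. The 100 evaluable patients do not follow from the article's own inputs, and adjustment within the range shown does not repair that.

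**What to change.** In Statistical analysis, state four things:

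- The primary estimate is the arm difference in mean 6 h NRS from a linear model with arm, center and a short fixed list of covariates known before allocation. These are age, plus sex and planned resection type if the datasheet records them before allocation.
- The model's 95% CI is judged against the 1-point margin.
- The unadjusted difference is reported as a sensitivity analysis.
- The list and its categories are fixed, with a date, before outcome data are examined by arm.

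The cost is a short addition to the text, one model, five degrees of freedom out of 106, and about 2 power points if the covariates explain nothing. The sample-size shortfall needs to be dealt with separately.

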## Methods/design

### Trial design

This is a prospective, randomized, controlled, two-arm, multicenter, single-blind study evaluating the efficacy of postoperative analgesic management of WI versus WI plus L-TAP in the context of laparoscopic colorectal surgery. Randomization is at the patient level, and participants are randomized 1:1 to receive either WI alone or WI plus L-TAP.

The protocol aim is to demonstrate the noninferiority of WI compared with WI plus L-TAP in terms of effectiveness of pain management. We are supposing a noninferiority limit for pain assessment measured according to the numeric rating scale (NRS) of 1 of 10 as the largest difference that is clinically acceptable, so that a difference in NRS greater than 1 would matter in practice.

Patients enrolled in this trial are asked to report their pain according to NRS at rest and during cough or movements, together with the occurrence of PONV at 6 h from surgery and twice daily until POD 3. Contemporarily, the amount of rescue analgesics is recorded, with patients being educated to request additional analgesic drugs when their pain is greater than NRS 4. Resumption of gut functions, evaluated as the passage of gas and stool as well as the ability to tolerate liquid and soft diet, is also considered together with the postoperative length of hospital stay. The study flow diagram and time of collection of outcomes are shown in Figs. 1 and 2, respectively.

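### The printed noninferiority rule (lower 95% limit above 1) is wrong whichever way the difference is taken

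*Protocol article*

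**What the plan says.** The Statistical analysis section gives one confidence-interval criterion for the primary outcome, pain on the NRS at 6 hours: "noninferiority is determined when the lower boundary of the 95% CI is > 1". It does not say which arm is subtracted from which, and no other section gives a different criterion.

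Three other statements in the protocol article fix what the criterion has to do:

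- **Scale** (Primary endpoint): "The NRS is graded from 0 to 10, where 0 refers to “no pain” and 10 to “worst pain". A higher score is worse.
- **Hypothesis** (Sample size calculation): "The null hypothesis is that WI is inferior to WI plus L-TAP". The trial must reject inferiority of WI.
- **Margin** (Sample size calculation): "The noninferiority limit of NRS 1 has been intended to be the largest difference that is clinically acceptable". Trial design gives the same limit and adds "so that a difference in NRS greater than 1 would matter in practice".

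**The concern.** Taken together, the scale, hypothesis and margin mean that noninferiority requires ruling out that WI is worse by more than 1 point. The confidence limit that matters is therefore the one on the side where WI does badly, and it must fall short of the margin. The printed rule takes a lower limit and asks it to exceed +1, which does not match that requirement under either direction of subtraction.

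This sentence alone decides the primary claim. The article says that a finding of noninferiority would call the usefulness of TAP block into question. Read literally in one direction, the rule would support that conclusion with data showing WI to be clearly worse. Read literally in the other, it sets a bar that a truly noninferior WI would almost never clear.

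**Working it through.** **Inputs.** From Sample size calculation: "NRS is 2.8 (1.9) for the WI plus TAP block group and 3.1 (1.9) for the WI group", so the SD is 1.9 in both arms and the planned difference, WI minus combination, is 3.1 − 2.8 = +0.3. The margin is 1. There are 100 evaluable patients, 50 per arm at 1:1 allocation. The 95% CI is from Statistical analysis.

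**Step 1: logic.** Let D be the true difference WI minus (WI plus L-TAP), so positive D means WI is worse. The null hypothesis is D ≥ 1 and noninferiority is D < 1.

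| Difference used | A lower limit above +1 shows | Correct condition |
|---|---|---|
| WI − (WI plus L-TAP) | D > 1: WI worse by more than the margin | upper limit < +1 |
| (WI plus L-TAP) − WI | D < −1: WI better by more than 1 point | lower limit > −1 |

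In the first row the rule attaches the label of noninferiority to proof of the null. In the second it asks for superiority by more than 1 point. The two correct conditions are the same test.

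**Step 2: interval width.** SE = SD × √(2/n) = 1.9 × √(2/50) = 0.38. With t(0.975, 98 df) = 1.984, the half-width is 1.984 × 0.38 = 0.754.

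- Printed rule on WI minus combination: the observed difference must exceed 1 + 0.754 = 1.754.
- Corrected rule: the observed difference must be below 1 − 0.754 = 0.246.

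**Step 3: probability of declaring noninferiority.** With T following a noncentral t distribution with 98 df and noncentrality (D − 1)/0.38:

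- printed rule, WI minus combination: P(T > 1.984)
- corrected rule: P(T < −1.984)

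For the printed rule on the reverse difference, the noncentrality is (−D − 1)/0.38 and the probability is again P(T > 1.984).

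| True D (WI minus combination) | Printed rule, WI − combination | Printed rule, combination − WI | Corrected rule |
|---|---|---|---|
| 0 | 0.0000025 | 0.0000025 | 0.741 |
| +0.3 (planned) | 0.000077 | 0.00000004 | 0.446 |
| +1 (at the margin) | 0.025 | below 0.000001 | 0.025 |
| +2 | 0.741 | below 0.000001 | 0.0000025 |

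On WI minus combination, the printed rule is met more often the worse WI is. The corrected rule is met less often as WI worsens, and its error is 2.5% at the margin, as a noninferiority test based on a two-sided 95% CI should have.

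**Step 4: sensitivity to the sample size.** With all 54 per arm analysed, the SE is 1.9 × √(2/54) = 0.366. Using 1.96 in place of t, the half-width is 0.717. The printed rule on WI minus combination then needs an observed difference above 1.72, and its probability at D = +2 is 0.78. The corrected rule needs an observed difference below 0.28 and gives 0.78 at D = 0 and 0.48 at D = +0.3. The conclusion does not depend on which n is used.

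**The case against.** The strongest objection is that this is a slip with a recoverable meaning. For the reverse difference, a lower limit above −1 is exactly right, so one lost minus sign, in writing or in typesetting, would explain the sentence. The margin, hypothesis, scale and expected means are all stated elsewhere, and an analyst reading them together would be unlikely to call WI noninferior when the interval for its excess pain lies wholly above 1. The 74% figure then describes a rule that the authors probably never meant to apply. It also holds only for WI minus combination; under the reverse subtraction the rule is far too strict and would not pass an inferior WI.

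Much of this stands. A lost minus sign is plausible, the consequence does depend on the unstated direction, and a condensed article may leave the direction of subtraction to the full protocol, so that omission alone would not be a fault. But the article does more than omit a detail: it states a threshold that is wrong in both directions. Either an upper limit below +1 or a lower limit above −1 would repair it, and they agree only once the subtraction is defined. A reader should not have to reconstruct the criterion by which the primary result is judged.

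**Conclusion.** The concern holds: the decision rule for the primary outcome is wrong as written. This follows from the article's own scale, margin and null hypothesis and needs no outside assumption.

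The size of the effect rests on the planning SD of 1.9, 50 per arm and approximate normality of the mean difference. On that basis, at the planned difference of 0.3 the printed rule would be met with probability below 0.0001 under either subtraction, against 0.446 for the corrected rule. If the difference is WI minus combination, the sign that matches the planning values, the printed rule would also call WI noninferior 74% of the time when WI is 2 points worse.

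The 0.446 falls short of the stated 0.8 power. That concerns the sample size calculation, is a separate matter, and does not bear on this point.

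**What to change.** Replace the sentence in Statistical analysis with wording such as: *The treatment difference is the mean NRS at 6 hours in the WI arm minus the mean in the WI plus L-TAP arm. WI is declared noninferior if the upper limit of the two-sided 95% CI for this difference lies below +1.* Defining the difference the other way and requiring the lower limit to lie above −1 is equally valid; one version should be chosen and used throughout. The section already says that the ITT and PP analyses should both support noninferiority, so the same rule should be named for both.

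The cost is one sentence, with no new data and no change of design. Recruitment ended in March 2019 and the article does not say whether analysis had begun. If it had not, the correction should be made before the data are analysed. If it had, a dated correction should be issued stating when it was made relative to the analysis.

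### The superiority rule for 6-hour pain equates the 5% level with P < 0.005, probably a misprint for 0.05 that should be corrected

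*Protocol article*

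**What the plan says.** In the protocol article, Methods/design, Statistical analysis, the paragraph on the primary outcome gives a noninferiority rule for the NRS score at 6 hours and then a superiority rule. Superiority is declared "when the two means are significant at the 5% level (two-sided *P* < 0.005".

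Two other statements bear on the threshold:

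- The preceding paragraph of the same section sets the general rule: "A two-sided *P* value less than 0.05 will be considered significant".
- The Sample size calculation section states: "A two-sided sample size calculation with 0.8 power and significance level of 0.05 reveals that 100 patients have to be included".

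The article describes no interim analysis, multiplicity adjustment or other device that would lower the superiority threshold to 0.005.

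**The concern.** The parenthesis should restate the 5% level as a P value. It gives a number ten times smaller. A P from 0.005 to below 0.05 is significant by the words of the sentence and not significant by its parenthesis, so the rule returns two conflicting answers.

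The threshold applies to the primary pain variable. If it stays uncorrected until the comparison between arms is known, whoever reports the trial can cite the protocol for either conclusion in that range. A later analysis plan could also follow either half and still claim to agree with the protocol.

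**Working it through.** **Inputs**

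- Thresholds: 0.05 (the 5% level) and 0.005 (the parenthesis), from Statistical analysis.
- Means and SD: the pain score "is 2.8 (1.9) for the WI plus TAP block group and 3.1 (1.9) for the WI group", from Sample size calculation. The SD is 1.9 and the planning difference is 3.1 − 2.8 = 0.3.
- Evaluable patients: 100, that is 50 per arm with 1:1 allocation (Allocation section). With nobody lost it is 54 per arm, because "With an estimated dropout rate of 8%, a sample size of 108 patients is required".

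**Step 1: the stated figure.** A two-sided test at the 5% level rejects when P < 0.05. The stated 0.005 does not reproduce: 0.05 / 0.005 = 10.

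**Step 2: the observed difference each threshold requires.** For an unpaired t test with n per arm, SE = SD × √(2/n), and the smallest significant difference is the critical t times SE.

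- n = 50: SE = 1.9 × √(2/50) = 0.38, with 98 degrees of freedom.
- P < 0.05: 1.984 × 0.38 = 0.754 points.
- P < 0.005: 2.872 × 0.38 = 1.091 points.
- n = 54: the same calculation gives 0.725 and 1.048 points.

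Observed differences of about 0.75 to 1.09 points (50 per arm), or 0.72 to 1.05 points (54 per arm), therefore fall between the two thresholds.

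**Step 3: how often a trial lands there.** The chance is the power at 0.05 minus the power at 0.005, from the noncentral t distribution and counting both directions. With 50 per arm:

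| True difference | Power at 0.05 | Power at 0.005 | Chance of falling between |
|---|---|---|---|
| 0 | 5.0% | 0.5% | 4.5% |
| 0.3 (planning value) | 12.2% | 2.1% | 10.1% |
| 0.7 | 44.6% | 15.8% | 28.8% |
| 1.0 | 74.1% | 41.0% | 33.1% |

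With 54 per arm the last column is 4.5%, 10.6%, 29.8% and 32.2%.

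**Step 4: what the threshold does not touch.** The noninferiority decision compares a confidence limit with the 1-point margin and does not use the superiority P value. The sample size was computed for a noninferiority test at 0.05. Neither changes when 0.005 becomes 0.05.

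**The case against.** The strongest reply is that any careful reader will see a stray zero. The words of the sentence, the general rule one paragraph earlier and the design significance level all give 0.05; only one parenthesis says 0.005. Superiority is also additional: the trial is designed and sized to show noninferiority of WI. Both points stand. They limit the severity, but they do not make the sentence correct, and a stated decision threshold should not depend on the reader's guess.

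Three stronger readings are tempting, and the document does not support them.

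- A reader might infer that results between the thresholds have no defined conclusion. They have two conflicting ones, and the rest of the document favours 0.05.
- A reader might object that the sentence names no arm. A two-sided rule needs none, because the sign of the difference shows which arm is favoured.
- A reader might judge the effect only at a true difference of 1.0 or more. That is at or beyond the noninferiority margin, where the ambiguity matters far more often than at the planning difference of 0.3.

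It is also tempting to rewrite superiority as a 95% confidence interval for the mean difference that excludes zero. That goes beyond what is needed. The same section allows a Mann-Whitney U test, whose P value need not agree with such an interval.

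**Conclusion.** The point holds as an internal inconsistency in a stated threshold, most probably a misprint for 0.05. It leaves a band of observed differences of about 0.75 to 1.09 NRS points in which the superiority rule contradicts itself. The chance of a result in that band is about 10% under the planning assumption and about 33% if the true difference is 1 point.

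These figures assume the protocol's SD of 1.9 in both arms, 50 evaluable patients per arm and an unpaired t test. With 54 per arm they hardly change; under a Mann-Whitney test they are only a guide.

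The document does not support reading this as a flaw in the main conclusion of the trial, since the noninferiority decision and the sample size do not depend on it. Severity: should-fix.

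**What to change.** In the superiority sentence of the Statistical analysis section, change the two-sided P < 0.005 to two-sided P < 0.05. It then agrees with the 5% level in the same sentence, the general rule and the design significance level.

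Issue this as a dated correction before the treatment comparison is seen. The Trial status section reports that recruitment was completed on 31 March 2019, so the date matters; if the comparison has already been seen, the correction should say so.

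The cost is one number. Sample size, data collection and the noninferiority analysis stay as they are.
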